### Intervention

The intervention is based on an online training course consisting of three modules. Each module can be completed within approximately 1 hour. Module 1 focuses on patient-centered doctor-patient communication, and points to typical communicative situations when treating patients with ARTI. Within the module, physicians are encouraged to reflect upon these situations and to question perceived pressure to prescribe antibiotics. Modules 2 and 3 deal with rational antibiotic use in the case of upper and lower respiratory tract infections. After passing the Continued Medical Education–accredited course, physicians receive posters and brochures on rational antibiotic use to display them in their practices or to use them during consultations. Physicians successfully completing the course receive a one-time allowance. In addition, physicians receive further reimbursement for up to 20 patients with ARTI per quarter, which they document as treated according to the strategies adopted after participating in the online training. In addition, participating physicians receive a feedback report on aggregated data on regional antibiotic prescribing patterns. Figures are compared between intervention and control groups. See Multimedia Appendix 1 for more details on each component and module of the intervention [14].

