### Sample Size

With respect to the primary outcome, a reduction of the physicians’ overall antibiotic prescription rate by 1% is assumed for RESIST (from 33.8% in the control group 1 to 32.8% in the intervention group). Without consideration of cluster effects, 2 × 34,865 patients are needed to show this effect with a power of 80% and a type I error of 5% (two-sided). Assuming an intracluster correlation (ICC) of 8% [16] and an average cluster size of 160 patients per practice, a design effect of 13.72 is determined. Overall, the sample size increases to 2 × 478,400 patients (956,800 patients in total). Thus, 2 × 2990 practices (5980 in total) are needed for the evaluation.

For the secondary outcome, a reduction of 3% in the physicians’ antibiotic prescription rate for ARTI is expected (from 30.5% in the control group 1 to 27.5% in the intervention group). Assuming a power of 80% and a type I error of 5% (two-sided), 2 × 3590 patients are required. With an ICC of 8% [16] and an average cluster size of 127 patients (diagnosed with ARTI) per practice, the sample size increases to 2 × 39,751 patients (79,502 patients in total). Hence, 2 × 313 practices are needed (626 practices in total). The sample size necessary to investigate the effect of the intervention on the primary outcome will be adequate to investigate its effect on the secondary outcome as well.

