### Data Collection, Completeness, and Quality

The trial is based on pseudonymized routine data provided by the Zi. The dataset is based on aggregated practice data. Information collected includes: age groups and sex of patients, ARTI diagnoses (grouped and individual diagnoses), antibiotic prescriptions, group affiliation of the physician (intervention vs control), region, level of urbanization, and type of medical insurance of the patient.

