### Statistical Methods

Data analyses will be performed in accordance with the STROBE statement [17]. For descriptive statistics, we will report the primary and the secondary outcome for the whole sample and by treatment allocation. Sampling units are practices. This evaluation is designed to confirm the two-sided primary hypothesis that the physicians’ antibiotic prescription rate after T1, regardless of the diagnosis, is lower in the intervention group than in control group 1. For investigating the primary outcome, we will use a negative binomial regression with the absolute number of annual antibiotic prescriptions as the dependent variable, the number of patients as the offset variable, and the antibiotic prescription rate before the introduction of RESIST as a covariate. To avoid bias, we will include region, specialization of the physician, proportion of male patients, proportion of different age classes (≤7 years, 8 to 18 years, 19 to 65 years, >66 years), proportion of insurance status (member, pensioner, noncontributory dependents), and the interaction between the proportion of male patients and region as additional covariates. The comparison between the intervention group and control group 1 is considered in a confirmatory manner. The comparison between the intervention group and control group 2 is additionally examined as a sensitivity analysis. The model for the secondary outcomes will be formulated in the same manner. The results will be represented as incident rate ratios with their 95% CIs and *P* values. Statistical analyses will be carried out with SAS, version 9.4 or the newer version (SAS Institute, Cary, NC, USA).

With respect to quality indicators (according to ESAC), sampling units are practices. The analysis will be carried out in the same way as the analysis of the primary and secondary outcomes considering the requirements of each indicator.

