## Discussion

With up to 3000 physicians participating in the program, RESIST is among the largest real-world interventions aiming at reducing inadequate antibiotic prescribing for ARTI in primary care. Long-term follow up of up to 21 months will allow for investigating the sustainability of the intervention.

As RESIST utilizes an open-label nonrandomized evaluation concept, potential bias has to be carefully addressed. Bias may arise from the fact that physicians most interested in reducing inadequate antibiotic prescriptions are also likely to be those most motivated to take part in RESIST. To counteract this, we make use of an attractive incentivization and reimbursement scheme. In addition, the inclusion of comparable practices not participating in the program (both among participating regions and among those not participating in RESIST) allows for control of this potential source of bias.

We will also minimize bias due to changed coding. For example, a clinically identical patient treated with antibiotics might be coded with lower respiratory tract infection initially but with pneumonia after the intervention, leading to an overestimation of the interventional effect. By measuring the overall antibiotic prescribing rate of antibiotics without regard to any specific disease as the primary outcome measure, we can exclude bias due to coding phenomena.

Last but not least, the RESIST program joins the ranks of other current initiatives to reduce inadequate antibiotic prescribing. Thus, contamination effects between the projects are possible. However, by including a high number of physicians and practices among half of all German states, we believe to be able to address this potential source of bias adequately.

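### The primary model omits the practice's baseline ARTI share, so the confirmatory rate ratio can be biased in either direction if that share still differs between arms after the planned adjustment

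*Protocol article*

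**What the plan says.** All references are to the protocol article.

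- **Enrolment and payment.** Under Recruitment, physicians join voluntarily in order of application. Under Intervention, those who complete the course receive a one-time allowance, and "physicians receive further reimbursement for up to 20 patients with ARTI per quarter".
- **Primary model.** Under Statistical Methods, a negative binomial regression takes the annual number of antibiotic prescriptions as outcome and the number of patients as offset. The pre-RESIST prescription rate is a covariate. The further covariates are introduced with a stated purpose: "To avoid bias, we will include region, specialization of the physician, proportion of male patients, proportion of different age classes", followed by insurance status and the interaction of sex with region. The comparison with control group 1 is confirmatory.
- **Data held.** Data Collection lists "ARTI diagnoses (grouped and individual diagnoses), antibiotic prescriptions" among the items available.
- **Selection.** The Discussion recognises that physicians already motivated to reduce prescribing may be the ones who enrol. It answers: "To counteract this, we make use of an attractive incentivization and reimbursement scheme". It also relies on comparable non-participating practices. Selection by ARTI caseload is not discussed.
- **Periods.** T0 is 2016 plus the first two quarters of 2017. T1 runs from the third quarter of 2017 to the first quarter of 2019.

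**The concern.** The comparison is nonrandomized, so control of confounding rests on the covariate list. The primary outcome includes ARTI prescriptions and therefore follows ARTI incidence, to a degree that depends on how much of a practice's work is ARTI. Two practices can have the same overall rate at T0 and different ARTI shares. If ARTI incidence then changes, their expected T1 rates separate without any programme effect, and the T0 overall rate cannot tell them apart.

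A course about ARTI with an ARTI-linked payment could plausibly attract practices whose ARTI share differs from that of control group 1. If some difference remains after adjustment, part of a seasonal change would be reported as a programme effect, or would hide a real one. The planned effect is small, so even a bias of one or two per cent would matter.

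**Working it through.** **Plan's own figures.** The sample size assumes a change "from 33.8% in the control group 1 to 32.8% in the intervention group", a rate ratio of 0.328/0.338 = 0.970 (log -0.0300). The two-proportion formula (two-sided 5%, 80% power) gives 34,866 per group; the article states 34,865. The design effect is 1 + 159 × 0.08 = 13.72. Then 34,865 × 13.72 = 478,348, and 478,348/160 = 2989.7, which rounds up to the stated 2990 practices per group. The calculation reproduces; it is needed here only for the reference ratio.

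**Season.** Q4 and Q1 quarters make up 3/6 = 50% of T0 and 4/7 = 57% of T1. Suppose ARTI incidence in those quarters is r times that in the others (assumed r = 2 to 3). Mean quarterly incidence is (3r+3)/6 in T0 and (4r+3)/7 in T1:
- r = 2: 1.571/1.500, a rise of about 5%
- r = 3: 2.143/2.000, a rise of about 7%

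**Bias with no programme effect.** Let f0 and f1 be the shares of T0 prescriptions due to ARTI in the control and intervention arms, and g the common relative change in ARTI incidence. The spurious ratio is (1 + g·f1)/(1 + g·f0). The documents give neither f nor g. With f0 = 0.45 assumed:

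| f1 - f0 | g = -20% | g = -10% | g = +10% | g = +20% |
|---|---|---|---|---|
| 0 | 1.000 | 1.000 | 1.000 | 1.000 |
| 5 points | 0.989 | 0.995 | 1.005 | 1.009 |
| 10 points | 0.978 | 0.990 | 1.010 | 1.018 |

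For example, (1 - 0.2 × 0.55)/(1 - 0.2 × 0.45) = 0.89/0.91 = 0.978. On the log scale the second row is 16-37% of the planned effect and the third 32-74%. Setting f0 to 0.30 or 0.60 changes little.

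**Does the T0 rate remove it?** A negative binomial model with patient offset and T0 rate was simulated (2 × 2990 practices, 160 patients each, true ratio 1, 20 replicates per scenario). In the column order above it gave 0.987, 0.993, 1.004 and 1.010 at 5 points, and 0.977, 0.989, 1.010 and 1.017 at 10 points. Adding the T0 ARTI share, here the share of prescriptions, returned 0.998-1.001.

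**Do the planned covariates act as proxies?** With a proxy explaining 25-50% of the variance in ARTI share and g = ±20%, the ratio was 0.983-0.995 (incidence down) or 1.004-1.014 (incidence up). That is about 14-58% of the planned log effect. Adding the share gave 0.9985-1.0005.

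**Dependence on how ARTI enters the overall rate.** Take an assumed ARTI share of patients s = 30%, the article's ARTI rate of 30.5% and overall rate of 33.8%.
- *Mixture:* each patient is either ARTI or not. The non-ARTI rate is (0.338 - 0.0915)/0.7 = 35.2%, above the ARTI rate. With the intervention arm 10 points higher and g = +20%, the arms move from 0.338 to 0.335 and from 0.333 to 0.330, a ratio of 0.997. Simulation calibrated to 33.8% gave 0.995-1.001.
- *Additive:* ARTI prescriptions come on top of other prescribing at 0.338 - 0.0915 = 0.2465 per patient. Then f0 = 0.0915/0.338 = 0.271. At s = 40%, f1 = 0.122/0.3685 = 0.331. For g = +20% the ratio is 1.0662/1.0541 = 1.011. Calibrated simulation gave about 0.990-1.025.

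Adding the T0 ARTI share returned 0.998-1.003 in all of these calibrated runs.

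**The case against.** The strongest reply is that no imbalance has been shown. A change in ARTI incidence common to both arms cancels when their shares are equal after adjustment, as the zero row of the table shows. Specialization and the age classes are sensible proxies for ARTI load, and both are in the model. This stands: the concern is conditional. The proxy runs show the bias reduced but not removed.

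The selection route is also weaker than it may look. A reader might infer that the programme pays most to practices with many ARTI patients. The documents do not support that, because the payment stops at 20 patients per quarter. The sample-size section assumes 127 ARTI patients per practice. If that figure is annual (the period is not stated), it is 127/4 = about 32 per quarter, already above the cap. The one-time allowance is not tied to caseload. What remains plausible is that practices with few ARTI patients are deterred, or that interest in an ARTI course goes with caseload.

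The size depends on inputs the documents do not give. Under the mixture reading with assumed shares of 20-50%, the contrast stays within 0.996-1.004, and its sign can reverse. Restricting the annual count to matching quarters would remove the calendar part of the incidence change, but the article does not say this will be done, and year-to-year variation would remain.

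**Conclusion.** The point holds in conditional form. The fixed covariate list leaves out a baseline characteristic that is available from the data held and related to the outcome, and that may be related to enrolment. The T0 overall rate does not fully stand in for it. With assumed differences of 5 to 10 points and incidence changes of 10 to 20%, the bias runs from near zero to about 1-2.5% against a planned ratio of 0.970. The direction is open. On the prescription-share and additive readings, if participants have the higher share, falling incidence flatters the programme and rising incidence hides its effect; with the lower share the reverse applies.

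Two stronger readings are tempting and not supported:

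- *Any change in ARTI incidence biases the ratio.* It does so only if ARTI share differs between arms after adjustment, and the article gives no evidence either way.
- *The bias can equal the whole planned effect.* One can reach that with a 30% share, a 30.5% ARTI rate and a 10% non-ARTI rate. Those inputs imply 0.3 × 0.305 + 0.7 × 0.10 = 16.2% overall, against the article's 33.8%. The largest simulated figures also include the effect of an imprecise T0 rate, which appears even with no incidence change. In the additive case above, the incidence change alone accounts for 1.011 of a simulated upper end of about 1.025.

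**What to change.** Add the practice's T0 ARTI share to the covariates of the primary model, defined as patients with a Table 1 code divided by all patients, from T0 data only. A T1 share should not be used: the intervention and changes in coding after training could alter it, and the Discussion sets out to keep coding changes out of the primary result. Tabulate the T0 share by group, so that readers can see whether the arms differ.

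The cost is one more parameter and some collinearity with age mix and specialization, which is minor with thousands of practices. No new data are needed. Because the article reports that analysis began in February 2020, the change should be dated. If it is made after outcome results by group were seen, report it beside the planned model and label it as such.

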## Methods

### Study Design

As RESIST is primarily a real-world project aiming to address as many participants as funding allows, it is evaluated in the form of a nonrandomized controlled trial. Patient and physician data are retrieved from routine health care data used by the Central Research Institute of Ambulatory Health Care in Germany (Zi). The Zi continuously analyzes prescription and diagnoses data on behalf of all German regional Associations of Statutory Health Insurance Physicians. The data analyzed include information on diagnosis as coded in practices and prescriptions as collected in pharmacies. Physicians not participating in the program serve as controls, either among the 8 statewide participating Associations of Statutory Health Insurance Physicians (control group 1) or among the federal states not eligible for participation in RESIST (control group 2). Antibiotic prescription rates before the intervention (T0: 2016, 1^st^ and 2^nd^ quarters of 2017) and after the intervention (T1: 3^rd^ quarter of 2017 until 1^st^ quarter of 2019) are compared.

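### Level of urbanization is in the dataset but not in the primary model's covariate list, so confounding by practice location may remain; the age classes also need a small wording correction

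*Protocol article*

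**What the plan says.** Study Design says of the program that "it is evaluated in the form of a nonrandomized controlled trial". Under Recruitment, physicians in eight named states and regions enrol voluntarily, in order of application. Control group 1 consists of non-participants in those same regions.

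Data Collection, Completeness, and Quality states that "The dataset is based on aggregated practice data". It opens its list with "Information collected includes: age groups and sex of patients" and closes it with "region, level of urbanization, and type of medical insurance of the patient".

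Statistical Methods then sets out the confirmatory model. It is a negative binomial regression with the number of patients as offset and "the antibiotic prescription rate before the introduction of RESIST as a covariate". The further covariates are introduced with "To avoid bias, we will include region, specialization of the physician, proportion of male patients", continue with "proportion of different age classes (≤7 years, 8 to 18 years, 19 to 65 years, >66 years", and end with "proportion of insurance status (member, pensioner, noncontributory dependents), and the interaction between the proportion of male patients and region as additional covariates". Urbanization does not appear. The secondary outcomes use a model of the same form.

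**The concern.** When physicians choose whether to take part, the covariates in the model are the main stated protection against confounding. The Discussion concedes self-selection and relies on comparable non-participating practices, but the article describes no matching. Region, age, sex and insurance type all pass from the data list into the model. Urbanization is the one location or population descriptor that is held and then left out. The covariates are listed down to a single interaction term, so this is a stated choice rather than a detail left to another document.

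The target effect is small: 33.8% in control group 1 against 32.8% in the intervention group. If urban and rural practices differ both in uptake and in how their prescribing changed over the study period, part of that difference could enter the effect estimate. A larger sample would not remove it.

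Separately, the printed age classes jump from an upper limit of 65 to a class that starts above 66.

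**Working it through.** **1. The plan's own figures.** Inputs from Sample Size: 33.8% vs 32.8%, 80% power, two-sided 5%, intracluster correlation 0.08, 160 patients per practice.
- Two-proportion formula without continuity correction: 34,866 per group (stated 34,865).
- Design effect: 1 + (160 − 1) × 0.08 = 13.72 (as stated).
- 34,865 × 13.72 = 478,348 patients per group. Divided by 160, this is 2,989.7, so 2,990 practices, and 2,990 × 160 = 478,400 (as stated).
- Target rate ratio: 0.328 / 0.338 = 0.9704, a relative reduction of 2.96%.

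The figures reproduce, and nothing in this point changes them.

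**2. Data held against data used.**

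| Held (Data Collection) | In the primary model (Statistical Methods) |
|---|---|
| Age groups | Yes, as class proportions |
| Sex | Yes, as proportion male |
| Region | Yes, also in an interaction |
| Type of insurance | Yes, as status proportions |
| Level of urbanization | No, and no reason given |

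**3. What the listed covariates can and cannot do.** The region term compares practices within a region, so it leaves urban-rural differences inside that region untouched. The baseline rate should absorb most stable differences in prescribing level. It does not absorb a difference in change over time between urban and rural practices. That differential change is the route by which bias could remain.

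**4. Possible size, on assumptions only.** The documents give neither the urban-rural imbalance between groups nor any urban-rural difference in prescribing.

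First set: assume 30% of control practices are urban, a residual urban rate ratio g after the other covariates, and an imbalance d. The bias factor on the rate ratio is [1 + (0.30 + d)(g − 1)] / [1 + 0.30(g − 1)].

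| g | d = 0.02 | d = 0.05 | d = 0.10 |
|---|---|---|---|
| 1.02 | 1.0004 | 1.0010 | 1.0020 |
| 1.05 | 1.0010 | 1.0025 | 1.0049 |
| 1.10 | 1.0019 | 1.0049 | 1.0097 |

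The range is 0.04% to 0.97%. As shares of the target these are 0.04 / 2.96 = about 1% and 0.97 / 2.96 = about one third.

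Second set, deliberately high, with bias approximated as imbalance × difference in prescribing change:
- 0.15 × 0.05 = 0.75%, about a quarter of 2.96%.
- 0.20 × 0.10 = 2.0%, about two thirds of 2.96%.

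**5. What such a bias would mean for the test.** With 80% power at two-sided 5%, effect / SE is about 2.80. The planned SE is therefore about 2.96 / 2.80 = 1.06% in relative terms. If there were no true effect:

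| Bias | In SE units | Chance of P < 0.05 |
|---|---|---|
| 0.75% | 0.71 | about 11% |
| 1.0% | 0.95 | about 16% |
| 2.0% | 1.9 | about 47% |

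At the low end of the first set (0.04%) the bias is 0.04 / 1.06 = 0.04 SE, and the error rate is essentially unchanged. The direction is unknown; a bias of the opposite sign would hide a real effect.

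**6. Age classes.** Every whole-number age from 0 to 110 was tested against the four printed classes. Only age 66 falls in none, and no age falls in two. If age 66 is an assumed 0.5% to 2% of patients, that is 0.8 to 3.2 of 160 per practice, and the four proportions sum to 0.995 to 0.98.

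**The case against.** The strongest reply is that confounding has not been demonstrated. A reader might infer from the omission that the effect estimate is biased. The documents do not support that: nothing in them links urbanization to participation, or to prescribing once the baseline rate, region, specialty, age, sex and insurance mix are in the model. That objection stands, and the point is put as a possibility for that reason.

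The larger scenarios are also open to challenge. Differences of 5% and 10% in prescribing change are about 1.7 and 3.4 times the effect the program itself targets. They mark an upper region and are not expectations, so the low cases are shown beside them.

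A reader might also conclude that the age covariate is wrong. The text does not establish this. The last class most naturally means over 65 or from 66 upward, and age reaches the analysts as groups whose cut-points are not given. Even if the classes were coded as printed, one class serves as reference in a model with an intercept, and the unassigned patients would fall in with it. One year of age in an adjustment covariate should hardly move the treatment estimate.

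A third inference would be that physician specialty is missing from the data because the data list does not name it. That fails. The list is worded as inclusive, and it also omits the patient count that serves as the offset.

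Finally, analysis started in February 2020, so changing the confirmatory model is not free of consequence. This stands and shapes the fix.

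None of these replies explains why a location variable already held was left out.

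**Conclusion.** The concern holds in a limited form. In a self-selected comparison aimed at a relative difference of about 3%, the primary model leaves out a plausible confounder that is already in the dataset, without stating why. Confounding by practice location may remain, through urban-rural differences in change over time that neither region nor the baseline rate removes. Its size and direction are unknown. On the assumed inputs it runs from negligible (0.04%) through about one third of the target (0.97%) to about two thirds in a deliberately high case (2.0%). The error rates in the working also assume the planned sample size.

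The gap at age 66 is real in the text but is a minor wording matter.

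**What to change.** Add level of urbanization as a categorical covariate to the primary model and to the secondary models built in the same way. Because analysis began in February 2020, date the change and disclose it as a change to the confirmatory model. If the printed model is kept as primary, report the urbanization-adjusted model beside it as a labelled sensitivity analysis.

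The cost is a few extra parameters, small against the thousands of practices planned, and a declared departure from the published model. No new data are needed.

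As an editorial correction, check the age cut-points in the data extract and then write the last class as ≥66 years, so that the four classes cover every patient.
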